### 3. STUDY DESIGN

The study comprises a multicenter randomized parallel group open-label controlled intervention study in which premature born children will be randomized to receive complementary feeding at the corrected age of 12 weeks (intervention group) or at the corrected age of 17 weeks (control group). The pattern and structure of the complementary feeding will be according to the advice of the well baby clinics in the Netherlands, using a standardized nutrition schedule.

Stratification will take place according to center. In order to keep the number of subjects in the different groups closely balanced at all times block randomisation will be used. According to Altman the block size used is a multiple of the number of treatments. A blocked randomization schedule, using blocks of four, will be used. The randomisation will be computer generated by Castor edc. The research is funded by Nutricia Nederland. Nutricia Nederland will have no financial interest in this study, will not delivery food products, will not have veto in how publication of results will be. In case of any disagreement regarding publication of the data, the principal investigators ([name]) of the research will make the final decision. All data analysis will be supervised by the principal investigators.

#### Hospital visits for all preterm infants

The participants will be seen in the hospital before the start of complementary feeding, at corrected age 1 year and 2 years.

##### **1. Hospital visit before the start of complementary feeding**

- a. Information about the randomisation will be given. Parents receive a letter in which is stated when to start with complementary feeding
- b. Weight, height, head circumference, and SCORAD score will be measured
- c. A diary regarding the breast- or formula milk is taken
- d. The Baby Eating Behavior Questionnaire is taken

##### **2. Hospital visit at corrected age 1 year**

- a. Weight, height, head circumference, and SCORAD score will be measured

##### **3. Hospital visit a corrected age 2 years**

- a. Weight, height, head circumference, and SCORAD score will be measured
- b. Infant Toddler Quality of Life Questionnaire is taken
- c. Child Feeding Questionnaire is taken
- d. Ages and Stages Questionnaire is taken

All hospital visits will be combined with regular hospital visits if possible. We expect the preterm infants to have a regular hospital visit before the starting of complementary feeding and at 1 year. The hospital visit at the age of 2 years will be an extra hospital visit. In this study, measurements recorded for standard care and extra measurements taken as part of this study are used.

#### **Standard measurements during hospital visit:**

- Weight, height, head circumference

#### **Extra measurements:**

- SCORAD (**SCOR**ing**A**topic**D**ermatitis, a clinical tool used to assess the extent and severity of eczema).
- The eating behaviour (Baby Eating Behaviour Questionnaire (BEBQ)) is measured before the start of complementary feeding.
- Infant Toddler Quality of Life Questionnaire (ITQoL) or Pediatric Quality of Life Inventory (PedsQL) is measured at corrected age of 2 years.
- The Child Feeding Questionnaire (CFQ) will be measured at corrected age of 2 years.
- The Ages and Stages Questionnaire (ASQ) will be measured at corrected age of 1 and 2 years.
- Diary: Parents of all children are asked to complete three different diaries during the study period until age of 2 year.
  - Version 1 (Milk diary): A diary about the breast- or formula milk before the start of complementary feeding.
  - Version 2 (Start diary): A diary at the start of complementary feeding. Parents are asked to fill in when they give solid food for the first time, what kind of solid food they give and how much their child eats for the first time.
  - Version 3 (2 day diary): A 2-day diary method: Parents will be asked to fill in the food diary during two days, of which one day in the weekend. Parents are asked to do this at the age of 6 months, 9 months 1 year and 2 years.
- Microbiota: parents of all preterm children are asked to collect faeces at home at three different time points:
  - 10-11 weeks post term
  - 15-16 weeks post term

○ 20-21 weeks post term

If the parents give informed consent for collecting faeces, the preterm infants are part of group 2a. We will include a total of 150 patients for microbiota analysis. In case parents wish to attend the study without collecting faeces, they will be part of group 1 (see figure 1 and 2)

The measurements are collected at the hospital. If this is not possible, height and weight at the age of one and two years will be collected at the well baby clinics (with permission of the parents). The reach of the well baby clinics, part of the Child Health and Welfare service (JGZ), in the Netherlands is high. Ninety-eight percent of all the newborns and 95% of all the infants attend the well baby clinics. Regular visiting moments of the well baby clinics are given in table 2. The well baby clinics and the general practitioner will be informed about the study and the group in which the patients are allocated.

| Age                                  | Kind of contact        |
|--------------------------------------|------------------------|
| 4 th -7 th day | Home visit             |
| 2 th week                 | Home visit             |
| 4 th week                 | Visit well baby clinic |
| 8 th week                 | Visit well baby clinic |
| 3 months                             | Visit well baby clinic |
| 4 month                              | Visit well baby clinic |
| 6 month                              | Visit well baby clinic |
| 7,5 months                           | Visit well baby clinic |
| 9 months                             | Visit well baby clinic |
| 11 months                            | Visit well baby clinic |
| 14 months                            | Visit well baby clinic |
| 18 months                            | Visit well baby clinic |
| 2 year                               | Visit well baby clinic |
| 3 year                               | Visit well baby clinic |
| 3 years 9 months                     | Visit well baby clinic |

**Table 2:** Regular contact moments well baby clinics for children 0-4 years old in the Netherlands.

This study is registered at Nederlandse Trial Register (TC = 4939) and is being registered at clinical trials.gov.

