## **5. TREATMENT OF SUBJECTS**

### **5.5 Investigational product/treatment**

The intervention group will start complementary feeding at the corrected age of 12 weeks, when gross motor development should enable safe eating. The control group will start complementary feeding at the corrected age of 17 weeks. The pattern and structure of the complementary feeding will be according to the advice of the well baby clinics in the Netherlands, using a standardized nutrition schedule.

The parents will receive information direct after the randomization about the group allocation. One week before they are assigned to start with complementary feeding, they will receive a reminder by phone. If this is not possible an email or a letter by post will be send. Parents will have one week to start with complementary feeding, either at the corrected age of 12 weeks or at the corrected age of 17 weeks. Parents will receive detailed information about complementary feeding, what kind of food to start with, how often they have to give solid foods, and some recipes. The introduction of complementary feeding is divided in 4 steps: 1) introduction of vegetables, 2) introduction of fruits, 3) introduction of cereal, and 4) introduction of a warm meal. Parents receive information when to move on to the next step. The well baby clinics and attending pediatricians are informed about the group allocation and are asked to support parents to start with complementary feeding by the time they are allocated. They also receive the information that the parents received regarding how to start with complementary feeding. In case there is a reason not starting complementary feeding at the time of allocation, parents are asked to report this and the reason why not starting in the diaries. Furthermore, the diaries will point out at what time the parents started with complementary feeding.

For the term born children (control group B) there will be no intervention with complementary feeding.

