## 8.2 Randomisation, blinding and treatment allocation

Stratification will take place according to center. In order to keep the number of subjects in the different groups closely balanced at all times block randomisation will be used. According to Altman the block size used is a multiple of the number of treatments. A blocked randomization schedule (randomly permuting blocks of four and six) at a time will be used. The randomisation will be computer generated by Castor edc. Twins will be randomized as well; the first twin will be randomized into one of the two groups, the second twin will be assigned to the same group. Patients will be randomised to introduction of complementary feeding at the corrected age of 12 weeks (intervention group) and to introduction of complementary feeding at the corrected age of 17 weeks (control group) (1:1). The allocation of the timing of the start of treatment will not be blinded.

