### **8.3.4 SCORAD Index – Extra in this study**

The SCORAD Index is a clinical tool used to assess the extent and severity of eczema. To determine extent, the sites of affected eczema are shaded on a drawing body. The affected area is calculated as a percentage of the whole body. In addition a representative area of eczema is selected. In this area the intensity of the signs redness, swelling, oozing/crusting, scratch marks, skin thickening (lichenification) and dryness each is assessed as none (0), mild (1), moderate (2) or severe (3). Subjective symptoms (i.e. itching, sleeplessness) are scored by the caregiver using a visual analogue scale. Zero means no itch/no sleeplessness and 10 is the worst imaginable itch (or sleeplessness). The SCORAD Index will be used during all the hospital visits; before the start of complementary feeding, at 1 and 2 years of age.

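### No masked measurement is planned for the 1- and 2-year hospital visits, although nobody measuring then needs the arm; the risk is modest for BMI and greater for SCORAD

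*Protocol*

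**What the plan says.** Section 8.2 states: "The allocation of the timing of the start of treatment will not be blinded". Parents learn the arm at once (Section 5.5): "The parents will receive information direct after the randomization about the group allocation". The professionals around the child learn it too. Section 3, under the extra measurements, says "The well baby clinics and the general practitioner will be informed about the study and the group in which the patients are allocated", and Section 5.5 says "The well baby clinics and attending pediatricians are informed about the group allocation", so that they can support the allocated start.

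On who measures, Section 3 says only "The measurements are collected at the hospital", followed by a fallback: "If this is not possible, height and weight at the age of one and two years will be collected at the well baby clinics". Section 3 also says of the visits: "All hospital visits will be combined with regular hospital visits if possible". It expects the 1-year visit to coincide with routine care and the 2-year visit to be additional.

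Section 8.3.4 places SCORAD at the hospital visits. Extent and six sign intensities (none to severe) are assessed on examination. For the rest, "Subjective symptoms (i.e. itching, sleeplessness) are scored by the caregiver using a visual analogue scale", each from 0 to 10. No section describes a measurer who is kept unaware of the arm.

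**The concern.** An intervention that parents deliver themselves cannot be blinded to them, and clinics need the arm in order to support the start. That reason ends when the start windows close. The outcomes come months later, when knowledge of the arm serves no purpose for the person holding the measuring board or grading the skin.

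The protocol also puts the expected direction in writing. Section 4.3 expects more overweight after early introduction. Section 1.1.1 cites odds ratios of 3.49 and 2.94 for eczema with early solids. An assessor or parent who knows the arm and shares that expectation could lean the same way. At stake are a BMI cut-off with a low base rate and, more plausibly, a skin score made up of graded judgements and parental ratings.

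**Working it through.** **1. Who knows the arm, and who measures**

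- Well baby clinics: told the arm (Sections 3 and 5.5). They supply height and weight when the hospital cannot, and they do not take SCORAD. Knowledge of the arm is explicit here.
- Attending pediatricians: told the arm (Section 5.5). Visits are merged with routine ones where possible (Section 3), but the protocol does not name the hospital measurer. Knowledge of the arm is an inference here, weaker at the extra 2-year visit than at the 1-year visit.
- General practitioner: told the arm, but measures nothing for the trial.
- Parents: told the arm, and score two SCORAD items.

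**2. Whether the arm is still needed.** The late group starts at 17 weeks corrected age, and parents have one week to begin (Section 5.5), so the last window closes at 17 + 1 = 18 weeks. The earliest 1-year measurement is 52 − 6 = 46 weeks (six-week margin, Section 8.1.1).

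**3. The plan's own figures.** Inputs from Section 4.3: 6% versus 13%, significance level 0.05 (taken as two-sided), power 80%. With a pooled variance, n = [1.960·√(2·0.095·0.905) + 0.842·√(0.06·0.94 + 0.13·0.87)]² / 0.07² = 274.2, so 275 per group. Then 550/0.95 = 579. Both agree with the protocol. This point does not affect the sample size.

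**4. How sensitive the BMI cut-off is to an error in one arm.** The protocol gives no size for such an error, so these are assumed scenarios. Take 6% truly above the cut-off in both arms, 275 per arm and normally distributed BMI. If one arm is shifted by s SD, its observed prevalence is P(Z > 1.555 − s), and the two-sided 5% test rejects at this rate:

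| Shift s (SD) | Observed prevalence | False-positive rate |
|---|---|---|
| 0 | 6.0% | 5.0% |
| 0.02 | 6.2% | 5.2% |
| 0.05 | 6.6% | 6.0% |
| 0.10 | 7.3% | 9.3% |
| 0.20 | 8.8% | 23.7% |

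To express this in centimetres, assume a height of 87 cm, a mean BMI of 16.5 and an SD of 1.4 (range 1.2–1.6). None of these is in the protocol. The BMI change is 16.5·[(87/(87 − h))² − 1], where h is the shortfall in height:

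| Height read short in one arm | BMI change | Shift (SD 1.4) | Prevalence (SD 1.6 to 1.2) | False-positive rate (SD 1.6 to 1.2) |
|---|---|---|---|---|
| 0.25 cm | 0.095 | 0.07 | 6.7–7.0% | 6.5–7.7% |
| 0.5 cm | 0.191 | 0.14 | 7.6–8.2% | 11–17% |
| 1 cm | 0.386 | 0.28 | 9.5–10.9% | 33–54% |

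Small errors matter little. Only a consistent error of about half a centimetre or more, confined to one arm, would be a real problem. Section 10 says the planned size was not reached. With fewer children the same shift would bias prevalence equally but cross the significance threshold less often.

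**5. SCORAD.** No calculation is possible, because the protocol gives no weighting of the parts. Structurally, the parental items offer up to 2 × 10 = 20 scale points, all from people who know the arm. The six signs offer up to 6 × 3 = 18 grading points, by judgement. Section 10 allows the score to be continuous or categorical and does not separate the two sources.

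**The case against.** The strongest reply is that BMI is hard to bias. Sections 8.3.1 to 8.3.3 prescribe a stadiometer without shoes, weight in underwear without a diaper, and a fixed formula; the measurer does not assign the category. A uniform half-centimetre error in one arm, across centers and some 20 months after staff heard the allocation, has no support in the documents. Nor is a shared expectation among staff shown: Section 1.1.2 calls the literature conflicting, and Section 11.4 stresses benefits of early introduction. This stands, and it is why the BMI risk is called modest. The choice between recumbent and standing height in Section 8.3.1 leaves some discretion, but not much.

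Two further limits also stand. Masking cannot reach clinic staff who were told the arm earlier, or values already recorded. SCORAD is a secondary endpoint, and its scoring could be settled in an analysis plan that is not shown. Who measures and what that person is shown is trial conduct, however, and the protocol is where it belongs.

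A reader might also infer that in the roughly 80% of preterm children without eczema (Section 1.1.1 cites 19.9% with it) only parental scores can move the total. That does not follow. A prevalence from a cited cohort does not show that extent and intensity are zero in the remaining children of this trial, and dryness is itself one of the graded signs. Nothing shows either that parents of unaffected children would score differently by arm.

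**Conclusion.** The concern holds in a limited form. The protocol discloses the arm to the clinics that supply fallback height and weight and to attending pediatricians. It provides for no masked measurement at the 1- and 2-year hospital visits, although the need for the arm ended at about 18 weeks corrected age. The risk is modest for BMI and greater for SCORAD.

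A reader might infer that all staff who take the outcomes are told the arm. The text supports that only for the clinics; for hospital measurers it is an inference, since they are not named. A reader might also take the centimetre table as a forecast that the primary result will be biased. It is a sensitivity illustration resting on assumed height, mean BMI, SD, normality and a one-sided error, and at shifts of 0.05 SD or less the false-positive rate stays at or below 6.0%. This is an avoidable weakness worth correcting, and it does not invalidate the primary comparison.

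**What to change.** In Sections 8.2 and 8.3:

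1. For the remaining 1- and 2-year hospital visits, state that height, weight and SCORAD signs are recorded by existing staff who are not shown the allocation, and ask parents not to mention it. Flag well-baby-clinic values as unmasked and add a sensitivity analysis that excludes them.
2. Before any comparison by arm, specify the examiner-graded SCORAD part (extent plus intensity) as the between-arm eczema measure. Report the parental itch and sleep scores, and the full total, separately.

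The cost is an instruction to sites, a source flag in the data, one extra analysis and a documented amendment to the eczema measure; no visits or staff are added. Telling clinics and pediatricians the arm for the feeding start can continue. The downsides are that masking will sometimes fail, that it cannot cover outcomes already recorded or clinic fallback data, and that the full SCORAD total becomes supportive. The second change also matters for past visits, provided the component scores were kept and the choice is fixed before anyone sees results by arm.

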**Measurements for control group B (term born children)**

The term born infants will be enrolled in two hospitals, or obstetric practices and well baby clinics affiliated with the hospital, in which the preterm infants are also enrolled. The parents of the term infants will be informed with a brochure by the midwife, nurse or medical doctor during a obstetric practice visit, outpatient clinic/well baby visit or during the hospital stay/visit for the delivery. If parents give approval to the midwife or doctor, the midwife or doctor will inform the researcher or research nurse. They will contact parents by phone and provide additional information and give or send the information letter and informed consent form to the parents. Parents will be give at least one week to consider their decision after receiving the information letter and informed consent form. Informed consent will be taken by the researcher or research nurse. Treatment or follow-up of the term born child will not change depending on participation in this study. Parents will be given at least one week to consider the information before making the decision on participation. If there are no further questions, informed consent will be taken.

Parents of the term born infants are asked to:

- Fill in the BEBQ and a questionnaire regarding parental characteristics (see 8.1.3) when their child is 3 months old
- Send information to the researchers about the growth parameters (length, weight, head circumference) of their child at 3 months, 1 year and 2 years old, obtained at the well baby clinic
- Fill in four food diaries when their child is 6 months, 9 months, 12 months and 24 months old

## **4. STUDY POPULATION**

### **4.1 Population (base)**

Preterm infants born between 30 and 35/7 weeks gestational age

#### **4.1.1 Inclusion criteria**

- Preterm infants born between 30 and 35/7 weeks gestational age
- Informed consent from both parents

#### **4.1.2 Exclusion criteria**

- Small for Gestational Age (SGA) (<p2.3)
- Diseases interfering with stable growth
- Intestinal disorders (necrotizing enterocolitis needing surgery, short bowel syndrome, hirschsprung disease, inflammatory bowel disease)

- 
- Moderate and severe bronchopulmonary dysplasia (BPD) defined according to the international criteria
  - Kidney disorders
  - Congenital heart disease with hemodynamic consequences
  - Severe cow milk allergy (Samson score  $\geq 3$ )
  - Congenital anomalies Ear Nose Throat (ENT) area, esophageal and or tracheal, needing operative correction (e.g. cheilognatopalatoschizes, esophageal atresia)
  - Syndromal disorders (e.g. trisomie 21, PraderWilli)
  - Intra ventricular hemorrhage grade III or IV
  - No motivation of parents
  - No informed consent

## 4.2 Control population

The control population exists of preterm infants born between 30 and 35/7 weeks gestational age. These children will start with complementary feeding at the corrected age of 17 weeks. The structure of complementary feeding will be the same as the children who start with complementary feeding at the corrected age of 12 weeks.

### Control group B:

Control group B exists of term born infants.

The inclusion criteria for the term born children are:

- Term born infant (born between 37 and 42 weeks of gestational age)
- Written informed consent from both parents, or legal representative

The exclusion criteria for the term born children are:

- Small for Gestational Age (SGA) (<p2.3)
- Diseases interfering with stable growth
- Intestinal disorders (necrotizing enterocolitis needing surgery, short bowel syndrome, hirschsprung disease, inflammatory bowel disease)
- Moderate and severe bronchopulmonary dysplasia (BPD) defined according to the international criteria
- Kidney disorders
- Congenital heart disease with hemodynamic consequences
- Severe cow milk allergy (Samson score  $\geq 3$ )

- Congenital anomalies Ear Nose Throat (ENT) area, esophageal and or tracheal, needing operative correction (e.g. cheilognatopalatoschizes, esophageal atresia)
- Syndromal disorders (e.g. trisomie 21, PraderWilli)
- Intra ventricular hemorrhage grade III or IV
- No motivation of parents
- No informed consent

### 4.3 Sample size calculation

The sample size calculation for this study is based on previous reported effects. In a population based study Jingxiong et al reported that introduction of complementary feeding before the age of 4 months resulted in a 76% higher odds in developing overweight than children introduced to complementary feeding after 4 months. Overweight in this study was defined as weight-for-length/height  $\geq 2$ SD above the median of the WHO reference for sex, i.e. weight-for-length/height z-score  $\geq 2$ SD. A study by Young et al reported that excess weight gain (defined as gaining  $\geq 0.5$  in weight-for-age Z-score) between 4 to 6 months was associated with an odds ratio of 2.5 for overweight at 18-24 months. This led to the conclusion that rapid early weight gain, for example due to early weaning, could result in obesity since known post-natal risk factors for obesity are rapid early weight gain and early weaning. Based on these studies we expect that the introduction of early complementary feeding in children will result in a higher prevalence of overweight children at the age of 2 year in comparison to later introduction of complementary feeding. Based on the given odds ratio of 1.76 and 2.5 an odds ratio of 2.3 was used to calculate our sample size. In 2009, the prevalence of overweight was 8% in two year old children in the Netherlands. Overweight was determined by measuring the BMI. BMI was calculated as weight/height and expressed as kg/m^2. Overweight and obesity prevalence rates were calculated using International Obesity Task Force (IOTF) cut-of values. In this study, the same calculation and definition will be used. Information of the prevalence of overweight in premature infants is lacking. Bocca-Tjeertes et al has shown that preterm infants are a growth restraint compared to term infants. On the other hand, Euser et al found a greater fat mass normalized for weight in preterm infants. Given this contrasting information on preterm infants, a slightly lower prevalence of overweight of 6% was used to calculate the sample size. Using the odds ratio of 2.3, the intervention group will have a prevalence of overweight of 13%. With a 0.05 significance level and a power of 80% a minimal sample size of 275 patients per group is required to detect a significant increase in the prevalence of overweight. Loss to follow-up is

calculated to be 5%. This is based on the fact that 95% of all the infants attend the well baby clinics in the Netherlands. In case patients will not attend the hospital visits, the well baby clinics will be contacted for information about height and weight. This means that 579 children have to be included in the study, finalized by a number of 600 children.

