## 8. METHODS

### 8.1 Study parameters/endpoints

#### 8.1.1 Main study parameter/endpoint

The main study parameter of this study is the prevalence of obesity determined by measuring the BMI at the corrected age of 2 years, according to the IOTF cut-off value. In addition, BMI will also be determined before the start of complementary feeding and at the corrected age of 1 year. A variation of 6 weeks before and after the corrected age of 1 and 2 years will be accepted.

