### 8.6 Follow-up of subjects withdrawn from treatment

There will be no follow-up of subjects withdrawn from the study. Subjects withdrawn from the study still participate in the regular follow-up scheme for prematurity offered by the treating hospital.

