## 10. STATISTICAL ANALYSIS

Since the sample size was not archived, the data will be interpreted with caution. Data will be analyzed on an intention to treat basis. In addition, we will also perform a per protocol analysis, taking into account the attrition rate. In case of missing values we will use multiple imputation. For the per protocol analysis, the criteria for the start of complementary feeding will be 12-13 weeks for the early group and 16-17 weeks for the late group. A p-value of 5% will be regarded as statistically significant and results will be presented with 95% confidence intervals.

Categorical data will be presented in absolute numbers and percentages. If a metric variable is normally distributed results will be shown in mean and standard deviation (sd). If a metric variable is not normally distributed median will be used with the interquartile range.

Descriptive data on BMI will be compared with the most recent Dutch growth chart. For the primary study parameter, the prevalence of obesity, the percentage of patients that develop overweight by using the IOTF will be calculated and intervention group and control will be compared including prevalence ratios with 95% confidence intervals. Furthermore, BMI and BMI z-scores between the intervention and control group will be compared as continuous variables.

The results of the questionnaires (BEBQ, CFQ, ITQoL / PedsQL, ASQ) will be analysed according to the scoring tables attached to the questionnaires. Allergy will be scored by a SCORAD form and can be presented as continuous or categorical variable. All blood and faeces results will be analysed as continuous or categorical variable. The diary results will be analysed as a continuous variable.

For all sub-objectives (as formulated in chapter 2), the intervention group and control group will be compared to determine the effect of early versus late introduction of complementary food, using a independent t-test or nonparametric test. For subgroup analysis, i.e. for children with respiratory problems or tube feeding, logistic regression will be used.

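### The clinic fallback behind the 5% loss figure is not reconciled with the corrected-age window at 2 years, and section 8.6 adds avoidable missing outcomes

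*Protocol*

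**What the plan says.** **Loss assumption.** Section 4.3 fixes the prevalence in the late group first: "a slightly lower prevalence of overweight of 6% was used to calculate the sample size". For the early group it applies an odds ratio of 2.3 and rounds to 13%. The resulting requirement is: "With a 0.05 significance level and a power of 80% a minimal sample size of 275 patients per group is required". It then allows 5% for loss, arrives at 579 and rounds up to 600. The 5% is taken from the 95% of infants who attend well baby clinics, and it works through a fallback: "In case patients will not attend the hospital visits, the well baby clinics will be contacted for information about height and weight". Section 3 repeats the fallback for ages one and two years, without saying whether those ages are corrected. It also says that the 2-year hospital visit is additional to regular care.

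**Window.** Section 8.1.1 sets the primary BMI at corrected age 2 years and adds: "A variation of 6 weeks before and after the corrected age of 1 and 2 years will be accepted".

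**Clinic schedule.** Table 2 in section 3 is captioned "Regular contact moments well baby clinics for children 0-4 years old in the Netherlands". It starts with a home visit on days 4 to 7. Its later contacts include 11, 14 and 18 months, 2 years and 3 years. Corrected age is not mentioned.

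**Withdrawal.** The heading of section 8.6 speaks of withdrawal from treatment, but its text reads: "There will be no follow-up of subjects withdrawn from the study". The section adds that these infants stay in their hospital's regular prematurity follow-up. Section 8.4 lets the investigator withdraw an infant for urgent medical reasons. Section 10 states: "Data will be analyzed on an intention to treat basis", with multiple imputation for missing values.

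**The concern.** The fallback matters most at the primary time point, because the 2-year hospital visit is the one that is not part of regular care. If the clinic sees the child at two years from birth while the endpoint is dated from term, the more preterm infants may be measured too early to count. An attendance rate then does not translate into a rate of evaluable outcomes. Section 2 also plans an analysis of infants born before against after 32 weeks, and the earlier-born group has the largest gap.

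Separately, an intention-to-treat comparison is only as complete as its outcomes. Ending data collection for every withdrawn infant, including those the investigator withdraws, leaves outcomes to be imputed that might have been obtained with permission. The 5% makes no allowance for this.

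**Working it through.** **1. The plan's own figure.** Inputs from section 4.3: p1 = 0.06, p2 = 0.13, alpha 0.05, power 80%. Sidedness is not stated; two-sided is assumed because it reproduces the figure.

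n per arm = [1.960 × √(2 × 0.095 × 0.905) + 0.842 × √(0.06 × 0.94 + 0.13 × 0.87)]² / 0.07² = (0.8127 + 0.3465)² / 0.0049 ≈ 274.3, so 275. This matches.

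Inflation: 2 × 275 / 0.95 = 578.9, so 579, rounded to 600. This matches too. The arithmetic is right; only the 5% input is in question.

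**2. Age correction.** Section 2 equates 17 weeks corrected with 27 weeks after birth at 30 weeks' gestation, so the offset is 40 − GA weeks.

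**3. The 2-year contact.** For a visit exactly on the second birthday, the shortfall from corrected 2 years is 40 − GA:

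| GA | Weeks short | Within 6 weeks? | Delay needed |
|---|---|---|---|
| 30+0 | 10 | no | 4 weeks |
| 32+0 | 8 | no | 2 weeks |
| 33+0 | 7 | no | 1 week |
| 33+6 | 6.14 | no | 1 day |
| 34+0 | 6.0 | yes, at the limit | none |
| 35+6 | 4.14 | yes | none |

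In the subgroup born before 32 weeks (30+0 to 31+6), the shortfall is 10 to 8.14 weeks, so the visit must run 4 to 2.14 weeks late.

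**4. Neighbouring contacts.** The 18-month contact is 26.1 weeks before the second birthday, so it is 26.1 + 4.14 = 30.2 to 26.1 + 10 = 36.1 weeks early. The 3-year contact is 52.2 weeks after it, so it is 52.2 − 10 = 42.2 to 52.2 − 4.14 = 48.0 weeks late. Neither can substitute.

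**5. The 1-year visit, for comparison.** Fourteen months is 60.87 weeks and one year is 52.18 weeks. The deviation is 60.87 − 52.18 − (40 − GA), which runs from −1.3 weeks (30+0) to +4.6 weeks (35+6). The 14-month contact is in window for every eligible infant, so the mismatch is confined to 2 years.

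**6. Slack in the target.** 1 − 550/600 = 8.3%. Power with 600 randomised, 6% against 13%, is Φ{[0.07√n − 0.8127] / 0.4117}:

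| Loss | Evaluable per arm | Power |
|---|---|---|
| 5% | 285 | 81.5% |
| 8.3% | 275 | 80.1% |
| 10% | 270 | 79.4% |
| 15% | 255 | 77.1% |
| 20% | 240 | 74.5% |

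**7. Illustration on assumed shares.** Let f be the share born before 34 weeks and m the share relying on the clinic alone; the protocol gives neither. If every such clinic visit fell on the birthday and was not used, loss = 0.05 + 0.95 × f × m. With f = 0.35 and m = 0.10 this is 8.3%; with f = 0.50 and m = 0.30 it is 19.3%. Power with 600 is then about 80% and 75%.

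**The case against.** Several stronger readings are tempting, and the protocol does not support them.

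- A reader might infer that every infant born before 34 weeks who relies on the clinic is lost. That requires the contact to count from birth and to fall on the birthday itself. The first is the natural reading of Table 2, but neither is stated. A visit one day to four weeks late is in window. Nor does any section say that an out-of-window BMI is discarded; section 8.1.1 says only what is accepted.
- A reader might infer a loss well above 5%. The share who miss the hospital visit and the gestational-age mix are not given, so the loss cannot be calculated. Rounding up to 600 already absorbs 8.3%.
- A reader might infer selective loss of families who abandon the allocated feeding time. Under section 5.5 those families record the reason and the actual start in the diaries. Section 10 defines a per-protocol set by start week, which presupposes that they remain in the intention-to-treat set. They are not withdrawn.
- A reader might see section 8.6 as contradicting intention to treat. Multiple imputation is planned, so the analysis is weakened rather than contradicted. The 2-year hospital visit is additional to regular care, so hospital records are not shown to hold that measurement; the clinic is the likelier source.
- The window problem depends on gestational age, which randomisation balances in expectation. No bias between arms follows from it.

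Section 10 also appears to say that the target sample was not reached (its wording is garbled). The power figures above therefore describe the planned trial. That limits the value of re-deriving 600, but each lost outcome costs more when the sample is smaller.

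What stands after all this: the fallback's timing is not tied to the primary window, and the 5% does not cover out-of-window measurements or withdrawals.

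**Conclusion.** The concern holds in limited form. At the nominal 2-year clinic contact, infants born before 34+0 weeks fall outside the stated window, by 0.14 to 4 weeks, and no other contact fills the gap. Clinic attendance of 95% is therefore not evidence of 95% evaluable primary outcomes. This rests on reading Table 2 as time since birth and on applying the 6-week window strictly.

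The effect on power is modest over plausible losses: 81.5% at 5% and 77.1% at 15%, had 600 been enrolled. The actual loss is unknown. The end of follow-up in section 8.6 is a separate, smaller source of avoidable missing data, and the mismatch between its heading and its text should be resolved. This is worth correcting because it is cheap, not because the trial's conclusion is shown to be at risk.

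**What to change.** 1. For infants who miss the hospital visit, ask the clinic to measure at corrected 2 years. Alternatively, accept the routine 2-year clinic measurement under a wider window stated in advance, for example −10 to +6 weeks around corrected 2 years. Classify BMI by exact age that day, stating whether that age is corrected, and add a sensitivity analysis restricted to 6 weeks either side. A lower limit of −10 weeks covers contacts on or after the second birthday only.
2. In section 8.6, limit the end of follow-up to families who withdraw consent for use of data. Otherwise retrieve 2-year height and weight with parental permission. Make the heading and the text refer to the same kind of withdrawal.
3. In section 4.3, say that 5% is an attendance figure that does not allow for out-of-window measurements or withdrawals, and show power over a range of losses.

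The cost is amendment wording, a records request and, under the wider window, a somewhat larger spread of measurement ages, which the sensitivity analysis would reveal if it mattered.
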